### Eligibility criteria

#### Participants

The included participants will be required to meet the eligibility criteria. Participants will be evaluated by professional researchers. For participants who meet the inclusion criteria, the researcher will discuss the informed consent form and explain the risks and advantages of participating in the study in detail. Written informed consent will be obtained prior to the participants’ enrolment. Then, the researcher will again check whether the participants meet the inclusion criteria, and the confirmed participants will be randomly assigned to the EA group, the SA group or the solifenacin group.

#### Inclusion criteria

Patients with OAB who meet all of the following will be enrolled in the trial:
Meet the diagnostic criteria of the ICS and AUA for OAB [1–3];Aged 18–75 years;Have suffered from OAB ≥3 months;Have an OABSS ≥6;Are voluntarily willing to sign informed consent.

#### Exclusion criteria

Patients who meet any of the following criteria will be excluded from the trial:
Frequency and urgency of urination occur secondary to other diseases (secondary OAB);Mixed urinary incontinence patients;Patients with uncontrolled symptomatic urinary tract infection;Pelvic organ prolapse ≥ degree II;Bladder urine residue ≥100 ml;Allergy to metal, fear of acupuncture, or cannot tolerate EA therapy;Allergy to solifenacin or have anti-muscarinic contraindications, such as urinary retention, gastrointestinal retention, myasthenia gravis, ulcerative colitis, and angle-closure glaucoma;Uncontrolled diabetes; severe heart, liver, kidney, or mental illness; or coagulopathy;Patients with a pacemaker;Pregnancy or lactation period or have pregnancy intentions in the next year;Drug treatment or acupuncture for OAB within 1 month;Participants in other research projects.

#### Withdrawal criteria

The withdrawal criteria will be as follows:
Severe side effects assessed by a urologist at each centre;Serious complications or other serious diseases during the study;Withdrawal consent by the patient.

### Randomization and blinding

After the 1-week assessment has been carried out and informed consent has been obtained, participants will be divided into the EA group, SA group or solifenacin group at a ratio of 1:1:1 due to the completely randomized block design of the hospital factor. Randomization will be generated by the central random system based on the computer network. Randomized numbers and groupings will be applied by research assistants who are not involved in the treatment or evaluation. Patients in the EA group and the SA group will be blinded, while those in the solifenacin group will be subjected to open trials. In the informed consent signed before the participants were enrolled, we will inform them that there are two types of acupuncture in addition to the drug group, and participants will be required to complete the entire trial cycle no matter which group they are assigned to. After the last treatment, the evaluation for the blinding of acupuncture will be tested within 5 min in the EA and SA groups. The results of this evaluation will be used to analyze the effect of blinding on the trial outcome measures. Efficacy evaluation and data entry will be performed by research assistants who are not involved in the grouping. The statisticians, outcome assessors, and physicians will be blinded to the allocation during data summarization.

### Procedure

After randomization, therapeutic assessment will be conducted at six time points: baseline and at the end of weeks 4, 8, 12, 20, and 32. Full-time evaluators will be responsible for filling out, issuing, recovering and recording the urination diary card and case report form (CRF) during the trial.

### Intervention

Participants randomized to the EA group will receive a standardized 30-min EA treatment; the SA group is similar to the EA group except in terms of the current, the size of the needle, and the depth of the needle insertion; the patients in the solifenacin group will be treated strictly following pharmaceutical guidelines. All acupuncture treatment sessions will be performed by Chinese medicine practitioners registered as acupuncturists and who have at least 2 years of clinical experience in acupuncture practice. No participants will receive any other treatments.

### Electroacupuncture (EA)

According to traditional Chinese medicine theory, the results of previous studies and the opinions of acupuncture experts at Guang’anmen Hospital, China Academy of Chinese Medical Sciences, the following main acupoints will be selected: BL23 (Shen Shu), BL33 (Zhong Liao), BL35 (Hui Yang), and SP6 (San YinJiao). All acupoints are bilateral. The locations of each acupoint conform to the standard defined by the World Health Organization [21].

After sterilizing the acupoint areas, for BL33, a needle will be inserted at a point 1 cm upwards and outwards from the 3rd posterior sacral foramina into the 3rd posterior sacral foramina in a slant and in an inward and a downward direction as well as at an angle of approximately 45–70 degrees to the midline using a 0.30 mm × 75 mm needle inserted approximately 60–70 mm deep. For BL35, a needle will be inserted (needle size 0.30 mm × 75 mm) approximately 60–70 mm deep at a slant in an outward and upward direction. For BL23 and SP6, needles will be directly inserted approximately 25–30 mm deep with 0.30 mm × 40 mm needles. The duration of reinforcing- reducing manipulation of twirling and rotating needle should be used for 1 min to achieve de qi (a composite of sensations including acid, hemp, bilge sensation, warm and pulse, these feelings may even travel along the meridians), which is recognised to be an essential component for acupuncture efficacy. Then electrodes from the EA apparatus will be attached transversely to the needle handles for bilateral BL33 and BL35 with a current intensity of 2 to 6 mA and with a current intensity of 1 to 2 mA for ipsilateral BL23 and SP6. All current intensities will be as high as can be tolerated. The current frequency will be a continuous wave of 10 Hz, and the stimulation will last for 30 min. First, EA will be applied for three sessions per week for a total of 4 weeks, followed by twice a week for 8 weeks a total of 28 sessions over a course of 12 weeks.

### Sham electroacupuncture (SA)

The non-acupoints will be located 2 cm outward for BL33, BL35, BL23 and SP6. After local skin disinfection, a 0.2 mm × 25 mm needle will be used for insertion at a depth of approximately 2–3 mm until the needle can stand erectly. The manipulation of the needle to de qi will not execute, and the current intensity will be 0.1–0.3 mA (slight electrical stimulation is perceived by the patient). The connection method for the electrode and the number of sessions of acupuncture will be the same as those for the EA group.

### Solifenacin

Solifenacin will be taken orally at a dose of 5 mg once daily for 32 weeks. It will be suggested that patients who can tolerate the drug should continue to take the drug; the drug should be withdrawn in cases of failure; and patients with severe adverse reactions should stop taking the medicine at any time, which will be recorded.

### Outcome measures

In this study, there will be one primary outcome and nine secondary outcomes. These are presented in Table 1. All adverse events will be recorded. The OABSS is widely used as a primary outcome measure in OAB studies, as it is safe and convenient and has been proven to have good reliability and validity in OAB [22]. The OABSS is comprised of 4 test items including frequency of urination, nocturia, urgency urinary incontinence and urgency episodes in 24 h. Total score ranges from 0 to 15, with scores of 3 to 5 indicating mild OAB, 6 to 11 indicating moderate OAB, and 12–15 indicating severe OAB. The secondary outcomes are based on 7-day bladder diaries and the OAB-q. A previous study suggested that 7-day bladder diary provided more accurate information regarding incontinence than a 3-day diary [23], in which we will evaluate the average episodes of 24 h urination, nocturia, urge incontinence and urgent urination changes from baseline. The OAB-q, with 33 questions about sleeping, anxiety, trouble in life and so on, is appropriate for assessing symptomatic distress or assessing the impact of OAB on health-related quality of life [24].

**Table 1 Tab1:** Outcome measures

	Outcome measure	Time point	Description	Statistics
Primary outcome	Change in OABSS from baseline to the end of week 12	Week 12	Calculated based on the OABSS.	Modified t-test
Secondary outcomes	Change in OABSS from baseline to the end of weeks 4, 8, 20, and 32	Weeks 4, 8, 20, and 32	Calculated in the same way as the primary outcome.	Covariance analysis or non-parametric test
	Proportion of participants with a decrease in the OABSS of ≥3	Weeks 4, 8, 12, 20, and 32	The number of patients with a reduction in OABSS ≥3 divided by the number of participants at baseline.	A chi-square test or Fisher’s test
	Change in 24 h urination/nocturia/urgency urinary incontinence /urgency episodes from baseline	Weeks 4, 8, 12, 20, and 32	The average 24 h urination/nocturia/urgency urinary incontinence /urgency episodes equal to the sum of urination/nocturia/urgency urinary incontinence/urgency episodes divided by 7.	Covariance analysis or non-parametric test
	Change in OABSS for each question from baseline	Weeks 4, 8, 12, 20, and 32	Calculated based on the OABSS for each question.	Covariance analysis or Non-parametric test
	Change in OAB-q from baseline	Weeks 4, 8, 12, 20, and 32	Calculated based on the OAB-q.	Covariance analysis or non-parametric test
	Descriptive analysis of emergency medications and other treatments and drugs used at baseline, during therapy and at follow-up.		A questionnaire will be completed by participants to collect information regarding their other treatments.	Descriptive statistics
	Evaluation of the blinding of acupuncture	Week 12	After the last treatment, the evaluation for the blinding of acupuncture will be tested within 5 min in the EA and SA groups	Descriptive statistics
	EA acceptance assessment	Week 12	After the last treatment, the acceptance of EA will be tested within 5 min with a 5-point scale (‘1’ indicates easily accept and ‘5’ indicates very difficult to accept). Average scores will be calculated.	A chi-square test or Fisher’s test
	Evaluation of the intervention expectation	Weeks 0 and 12	A questionnaire will be completed by participants to evaluate their expectations of the intervention.	A chi-square test or Fisher’s test

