#### Study design

This study will be a multi-centre, randomized, parallel group, and three-arm clinical trial. It will be conducted from September 2019 to June 2021 in 4 hospitals around China. If the study is not expected to be completed on time, 2 research hospitals will be added or replaced. Participants with OAB will be recruited via posters, television, websites and outpatients and will then be screened according to the eligibility criteria. A total of 420 participants will be ultimately enrolled. Prior to enrolment, all participants will voluntarily sign the informed consent form that has been approved by the ethics committee. Randomization will be performed centrally by the Clinical Evaluation Centre of the China Academy of Chinese Medical Sciences in Beijing, and eligible participants will be randomized to the EA group, sham electroacupuncture (SA) group or solifenacin group at a 1:1:1 allocation ratio. A randomization number will be applied after enrolment. The statisticians, outcome assessors, and participants in the EA and SA groups will be blinded to the allocation. A flowchart demonstrating an outline of the study is included in Fig. 1.

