### Statistical analysis

Statistical analysis will be conducted by independent third-party professional statisticians. We will use a modified t-test based on the retention of the effect method to analyse whether EA is non-inferior to solifenacin [26]. If the lower boundary of the confidence interval around the mean difference between the numbers in the EA group versus the solifenacin group exceed 50% of the mean difference between the numbers in the solifenacin group and the SA group, then non-inferiority will be claimed. The intention-to-treat (ITT, randomized participants) and per-protocol datasets (PP, ITT participants who received at least one treatment session) will be used to analyse the primary outcome. Missing data will be filled with a multiple imputation method under the missing-at-random assumption. Secondary outcomes will be calculated with observed values. Categorical data will be described by case number and percentage and will be analysed with Fisher’s exact test or the Chi-square test where appropriate. Continuous data will be described as the mean ± standard deviation, median, maximum and minimum values, and comparisons between groups will be conducted by covariance analysis or nonparametric tests where appropriate. A P (2-tailed) value less than or equal to 0.05 will be considered statistically significant. Statistical Package for the Social Sciences (version 13.0; SPSS; Chicago, Illinois, USA) will be used to perform the statistical analysis.

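### The responder outcome is tested without the hospital strata or baseline OABSS: a small, avoidable loss of efficiency if either predicts response

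*Protocol article*

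**What the plan says.** The Randomization and blinding section describes 1:1:1 allocation "due to the completely randomized block design of the hospital factor". The wording is awkward, but the natural reading is blocks within hospital. The Study design section places the trial "in 4 hospitals around China" and allows two hospitals to be added or replaced.

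Every participant has a baseline OABSS: the inclusion criteria read "Have an OABSS ≥6", and the Procedure section lists baseline among the assessment times.

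Table 1 (Outcome measures) defines the responder proportion as "The number of patients with a reduction in OABSS ≥3 divided by the number of participants at baseline", at weeks 4, 8, 12, 20 and 32, and gives its test as "A chi-square test or Fisher’s test". The Statistical analysis section says that categorical data "will be analysed with Fisher’s exact test or the Chi-square test where appropriate". For continuous data, "comparisons between groups will be conducted by covariance analysis or nonparametric tests where appropriate", with no covariates named.

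**The concern.** Blocking by hospital balances the arms within each hospital. If response rates differ between hospitals, that balance removes some of the chance variation in the difference between arms. A crude chi-square still counts the removed part in its variance, so it rejects less often than its nominal level and loses power.

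Baseline OABSS is a separate matter. The article does not name it as a randomisation factor, so leaving it out does not shift the size of the test. It only forgoes precision, and only if baseline predicts response. A link is plausible: a fixed fall of 3 points is half the score of a patient entering at 6 but 3/13 = 23% for one entering at 13.

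At stake is some efficiency in the between-arm comparisons of one secondary outcome at five visits.

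**Working it through.** **The plan's own figure.** The Sample size calculation gives 420 patients, 80% power, α = 0.05 and 10% loss, for the primary non-inferiority comparison. The dropout step agrees: 420 × 0.9 / 3 = 126 evaluable per arm, and 126 / 0.9 = 140. No effect size or SD is given, so the 80% cannot be reproduced. No power or response rate is stated for the responder outcome, so what follows is a sensitivity range.

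**Inputs from the article.** 140 per arm (Table 1 divides by the number at baseline), 4 hospitals, blocking by hospital, two-sided 0.05.

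**Assumptions.** Two arms compared at a time, equal hospitals (35 per arm in each), and the prognostic strengths listed below.

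**Step 1: hospital only, large sample.** With hospital response rates p_h and mean p, the true null variance of the difference is (2/n) × mean[p_h(1 − p_h)]. The crude chi-square uses (2/n) × p(1 − p). Let r be their ratio, and set the effect so that the crude variance alone would imply 80% power. Then:

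- true size of the crude test = 2 × [1 − Φ(1.96/√r)]
- crude power = Φ(0.842/√r)
- stratified power = Φ(2.802/√r − 1.96)

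Example, rates 30, 43, 57 and 70%: mean p_h(1 − p_h) = (0.2100 + 0.2451 + 0.2451 + 0.2100)/4 = 0.2276; r = 0.2276/0.25 = 0.910; 1.96/√0.910 = 2.054; size = 4.0%.

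| Hospital rates (%) | r | True size, crude | Power, crude | Power, stratified |
|---|---|---|---|---|
| 45, 48, 52, 55 | 0.994 | 4.9% | 80.1% | 80.2% |
| 40, 47, 53, 60 | 0.978 | 4.75% | 80.3% | 80.9% |
| 30, 43, 57, 70 | 0.910 | 4.0% | 81.1% | 83.6% |
| 20, 40, 60, 80 | 0.800 | 2.8% | 82.7% | 87.9% |

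**Step 2: hospital and baseline, by simulation.** 4,000 trials per scenario. Assumed responder rates were 45% v 61.7% (80.3% power for two proportions at 140 per arm) and, under the null, 50% in both arms. The adjusted test is a logistic score test with hospital and baseline. Prognostic strength is in log-odds: the SD across hospitals, and the effect per SD of baseline.

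| Hospital SD | Baseline effect | Size, chi-square | Power, chi-square | Power, CMH | Power, adjusted |
|---|---|---|---|---|---|
| 0 | 0 | 5.0% | 80.3% | 80.3% | 80.6% |
| 0.5 | 0 | 4.6% | 80.7% | 82.8% | 83.0% |
| 0 | 0.5 | 4.4% | 80.4% | 80.4% | 83.5% |
| 0.5 | 0.5 | 4.0% | 80.7% | 82.5% | 84.3% |
| 1 | 0 | 2.8% | 82.2% | 87.6% | 88.1% |
| 0 | 1 | 4.9% | 80.4% | 80.4% | 87.7% |
| 1 | 1 | 3.3% | 81.5% | 86.0% | 92.0% |

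The Monte Carlo standard error of a size near 5% is √(0.05 × 0.95/4000) = 0.35 points. With only baseline prognostic, the chi-square and CMH sizes are identical (4.4% and 4.9%) and within two standard errors of 5%, so there is no sign of conservatism from omitting baseline. The simulated size of the adjusted test ran from 4.7% to 5.6%, so gains of a few tenths of a point should not be read as real.

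**Step 3: Fisher.** With no prognostic factor at all, Fisher had a size of 3.7% and power of 76.7% against 80.3% for chi-square. Across scenarios it cost about 3 to 4 points.

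**The case against.** The case against acting is that an unadjusted chi-square is a valid test for a secondary proportion, that its only error is towards caution, and that strata and covariates are often settled in an analysis plan that is not shown here. The validity point stands and limits this to a minor suggestion. The point about an unseen plan carries less weight, because the article states the test in two places; what is questioned is a stated choice, not a gap.

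It also stands that the article shows neither hospital nor baseline to be prognostic. Three of the hospitals are Western medicine hospitals and one is a traditional Chinese medicine hospital, which makes differences plausible but no more. Nor does the scale floor block response: a patient entering at 6 can fall by 6, twice the responder threshold.

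A reader might infer more than the article supports:

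- That only the binary outcome is unadjusted. The primary outcome's modified t-test names no covariate or hospital term, and the continuous secondary outcomes may go to a nonparametric test.
- That omitting baseline OABSS makes the test conservative. Only ignoring the hospital blocking can do that.
- That this is the trial's main clinical-response outcome. It is one of nine secondary outcomes.
- That the planned P values will be too large as a matter of course. If hospitals respond alike, the chi-square keeps its nominal size.

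**Conclusion.** The point holds as an efficiency issue of minor weight. The planned test ignores the factor used to block randomisation and a baseline score already collected. Under the assumed strengths, the gain from using them is zero if neither is prognostic, about 2 to 4 points of power with moderate effects (0.5 on the log-odds scale), and 5 or more only with strong ones (1.0, or hospital rates spread from 20% to 80%). Conservatism of the chi-square requires that hospitals differ in response and that blocking is within hospital. Choosing Fisher adds a further loss in tables of this size, whatever the prognostic effects.

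The figures also assume equal hospitals and 140 per arm. The Statistical analysis section plans observed values for secondary outcomes, which could bring the analysed number nearer 126 per arm. The ratio r in Step 1 does not depend on that number.

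The material does not support a claim of invalid inference: type I error is controlled either way, and the power stated for the primary outcome is not touched.

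**What to change.** In Table 1 and in the Statistical analysis section, replace the test for the responder proportion with one of the following, chosen in advance:

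- a Cochran-Mantel-Haenszel test stratified by hospital; or
- logistic regression with treatment, hospital and baseline OABSS, reported as a standardised risk difference.

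Keep Fisher's exact test for sparse tables, such as rare adverse events. State how hospitals that are added or replaced enter the strata.

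The cost is a line or two of wording and no new data. If neither factor is prognostic, the simulation shows no power penalty. A conditional odds ratio is harder to read than a difference in proportions, and the standardised risk difference avoids that at the price of one further computing step. The change should be dated and made before unblinding; the Trial status section reports 23 participants recruited when the article was written.

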### Sample size calculation

The sample size will be calculated based on previous studies conducted by Zhao Y et al. [14, 25]. A sample size of 420 patients will provide 80% power (α = 0.05) to detect a non-inferiority effect of EA therapy on the primary outcome, assuming a 10% loss. The non-inferiority margin will be 50% of the comparative efficacy between SA and solifenacin. The non-inferiority margin will be set based on our hypothesis that EA will be associated with at least 50% of the difference in efficacy of solifenacin compared with SA.

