### Measures to improve compliance

Establishing a good relationship between doctors and patients, and providing participants with subsidies for transportation costs. A patient manual for regular short message services will be used to remind patients to complete the bladder diary.

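### Table 1 divides diary totals by a fixed 7, so a partly filled diary understates that visit's 24 h average and distorts the change from baseline

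*Protocol article*

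**What the plan says.** Under Outcome measures, the article states: "The secondary outcomes are based on 7-day bladder diaries and the OAB-q". From the diaries, "we will evaluate the average episodes of 24 h urination, nocturia, urge incontinence and urgent urination changes from baseline". Table 1 then gives the derivation: each 24 h average is "equal to the sum of urination/nocturia/urgency urinary incontinence/urgency episodes divided by 7". The divisor is a constant. Neither the table nor the text mentions completed days, a minimum number of days or a different divisor for a partly filled diary.

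Diaries are assessed at "baseline and at the end of weeks 4, 8, 12, 20, and 32" (Procedure), so a blank day can fall at baseline or at any follow-up visit.

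Two sentences under Statistical analysis bear on gaps in the data. The general rule is: "Missing data will be filled with a multiple imputation method under the missing-at-random assumption". For these outcomes, however: "Secondary outcomes will be calculated with observed values". Under Measures to improve compliance, text messages "will be used to remind patients to complete the bladder diary".

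**The concern.** Because the article writes out a formula, this is more than a detail left open. An average described only as a daily mean from the diary would have left the handling of blank days to the analysis plan. A sum divided by 7 settles it, and settles it wrongly for any diary with fewer than seven completed days: the blank days add nothing to the numerator but stay in the denominator.

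The error would also be hard to see. A five-day diary still yields a sum and therefore a number. That number looks like an observed value and would not be flagged as missing, so neither the imputation rule nor the observed-values rule clearly catches it. Reminders can reduce the number of blank days but do not change how the remaining ones are scored.

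Four diary measures at five follow-up times are exposed, which is 4 x 5 = 20 visit-level results for each pair of arms. The Abstract lists these measures among the secondary outcomes that it names.

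**Working it through.** **Inputs.** Diary length of 7 days and fixed divisor of 7 (Outcome measures and Table 1). Endpoint: change from baseline in the 24 h average (same place). The article gives no episode rates and no diary completion rates, so the rates below are assumptions for illustration. The sample size of 420 does not enter this point.

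**The plan's formula for a complete diary.** With a true rate of m episodes per day and seven completed days, the sum is 7m, and 7m/7 = m. The formula is right in this case.

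**An incomplete diary.** With k completed days that resemble the blank ones, the sum is k x m. The stated formula returns m x k/7, an understatement of 1 - k/7:

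- k = 6: 1 - 6/7 = 14.3%
- k = 5: 1 - 5/7 = 28.6%
- k = 4: 1 - 4/7 = 42.9%

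Dividing by k instead returns m whatever k is.

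**Change from baseline.** Let b denote baseline and f follow-up. The computed change is m_f x k_f/7 - m_b x k_b/7. Its error against the true change m_f - m_b is

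m_b x (7 - k_b)/7 - m_f x (7 - k_f)/7.

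Blank baseline days push the result upward (worsening) and blank follow-up days push it downward (improvement). For urination at an assumed 12 per day at baseline:

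| Days completed, baseline / follow-up | No true change (12 to 12) | True change -2.00 (12 to 10) |
|---|---|---|
| 7 / 7 | 0 | -2.00 |
| 7 / 6 | -1.71 | -3.43 |
| 7 / 5 | -3.43 | -4.86 |
| 6 / 7 | +1.71 | -0.29 |
| 5 / 7 | +3.43 | +1.43 |
| 6 / 6 | 0 | -1.71 |
| 5 / 5 | 0 | -1.43 |

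For example, 7 / 6 with a true fall gives 10 x 6/7 - 12 = 8.57 - 12 = -3.43, and 6 / 6 gives -2.00 x 6/7 = -1.71.

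The error scales with the rate. With no true change, one blank follow-up day gives 3 x (6/7 - 1) = -0.43 at 3 episodes per day and 1.5 x (6/7 - 1) = -0.21 at 1.5 per day.

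**Between arms.** Suppose two arms have the same true rates and the same baseline completeness, and differ by an average of d completed days at follow-up. The spurious difference is then m_f x d/7. With an assumed 12 per day and d = 1, this is 12/7 = 1.71 per day, and smaller d scales in proportion. With d = 0 there is no spurious difference, but a true difference at follow-up is multiplied by k_f/7.

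**The case against.** The best defence is that the table entry describes the intended case. A seven-day sum divided by seven is the daily average, the entry is a short description in a condensed article, and handling of partial diaries is often set in an analysis plan, which is not shown here. The observed-values sentence can even be read as limiting the formula to days actually recorded, since entering a blank day as zero would itself be an imputation. That reading is possible, but the article does not state it. As long as the constant divisor stands, a programmer who follows Table 1 will score blanks as zero, and an analysis plan that did otherwise would depart from the published definition.

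A reader might go further and infer that every blank day shows up as improvement, so that the diary results are biased toward benefit. The documents do not support this. A blank baseline day produces apparent worsening, and equal gaps cancel when nothing has changed. The article gives no completion rates and does not say that completeness falls after baseline. The use of reminders does not establish it.

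A reader might also infer a bias between arms, because acupuncture patients attend two or three times a week while solifenacin patients do not. This too remains unproven. The assessment schedule is common to all arms, dedicated evaluators issue and collect the diary cards (Procedure), completion of the case report form is supervised (Quality control), and the reminders are not limited to any arm. The attendance argument also ends with acupuncture treatment at week 12, so it does not carry over to weeks 20 and 32.

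**Conclusion.** The formula in Table 1 gives a wrong value for any diary with fewer than seven completed days in which episodes occurred, and nothing else in the article corrects it. The understatement at the affected visit is certain arithmetic if the formula is applied literally: 14% for one blank day and 29% for two, provided blank days resemble completed ones. The effect on the change from baseline can go either way, and its size in this trial cannot be computed because the article reports neither episode rates nor completion rates. Bias between arms depends on unequal completeness, which is a possibility and not a finding.

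The reach is limited to the four diary-based secondary outcomes. The OABSS, and with it the primary non-inferiority comparison, does not use this formula; nor do the OAB-q and the OABSS-based secondary outcomes. The point should be corrected because the error is hidden and the repair is simple, but it does not threaten the main conclusion of the trial.

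**What to change.** In Table 1, define each 24 h average as the sum of episodes over completed diary days divided by the number of completed days. Prespecify a minimum number of completed days for the average to count, at a threshold for the sponsor to set, and treat a visit below it as missing. Say how such missing visits are handled, given the observed-values rule for secondary outcomes. A sensitivity analysis restricted to complete seven-day diaries is optional.

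The diary or case report form must be able to tell a completed day without episodes from a blank day. This matters most for incontinence and urgency, where zero is a legitimate daily count.

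The cost is one table entry and the derivation program. No new data are needed if completed days can be identified, and the article reports only 23 participants recruited when it was written. The small downside is that some sparse diaries become missing. Dividing by completed days also still assumes that blank days resemble recorded ones, a weaker assumption than treating them as free of episodes.

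### The acceptance row of Table 1 summarises an ordered 1–5 score by its average but names a chi-square or Fisher test, which ignores the ordering and does not compare averages.

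*Protocol article*

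**What the plan says.** Table 1 (protocol article, Outcome measures) lists an EA acceptance assessment among the secondary outcomes. After the last treatment, "the acceptance of EA will be tested within 5 min with a 5-point scale", where 1 is the most acceptable end and 5 the least. The description closes with "Average scores will be calculated". The Statistics cell of the same row reads "A chi-square test or Fisher’s test".

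The Statistical analysis section gives two general rules:

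- For categories, the rule is: "Categorical data will be described by case number and percentage and will be analysed with Fisher’s exact test or the Chi-square test where appropriate".
- For measurements treated as continuous, the summary is built on means with standard deviations, plus the median and the extremes. For these variables, "comparisons between groups will be conducted by covariance analysis or nonparametric tests where appropriate".

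Elsewhere in Table 1, the changes in the OABSS total, the diary counts and the OAB-q are assigned "Covariance analysis or non-parametric test". The row for each separate OABSS question, also a short ordered item score, names the same pair. The significance rule is general: "A P (2-tailed) value less than or equal to 0.05 will be considered statistically significant".

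**The concern.** The acceptance row takes its summary from the rule for continuous data and its test from the rule for categorical data. It is the only row of Table 1 that states an average and pairs it with a contingency-table test. A trend version of the chi-square, or a split of the scale into two classes, would reconcile the row in part, but neither is stated. The article does not leave the test open for a later document. It names one, and that one does not fit the stated summary.

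A reader of the results would see average acceptance scores beside a P value that does not compare them. The P value could be very small with identical averages, or unremarkable when the scores have shifted. In the second case non-significance could be taken to mean equal acceptability. That would matter for the Discussion's suggestion that EA may become a reasonable option for patients.

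**Working it through.** The documents state no figure for this outcome, so there is nothing of the plan's own to reproduce.

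**Inputs from the article.** Five ordered scores; two-sided 0.05; 140 randomised per arm; 10% loss, so 140 × 0.90 = 126 evaluable per arm.

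**Assumed inputs.** A comparison of EA with sham (SA), the score distributions and the sizes of shift. None of these is in the documents.

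**1. The test ignores the ordering.** With equal arms, Pearson's statistic reduces to Σ(aᵢ − bᵢ)²/(aᵢ + bᵢ). Take counts for scores 1 to 5 of 50/35/20/12/9 and 35/35/25/17/14.

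- Averages: 273/126 = 2.17 and 318/126 = 2.52.
- Chi-square: 15²/85 + 0 + 5²/45 + 5²/29 + 5²/23 = 2.65 + 0 + 0.56 + 0.86 + 1.09 = 5.15 on 4 df, p = 0.27.
- Rank-sum p = 0.024; t-test and linear trend test p = 0.029.

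Attaching the score labels to the columns in another order leaves chi-square at 5.15 and p = 0.27, although in one such order the averages become 3.06 and 3.17.

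**2. The test does not compare averages.** Counts of 10/20/66/20/10 and 40/15/16/15/40 both average 3.00.

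- Chi-square: 30²/50 + 5²/35 + 50²/82 + 5²/35 + 30²/50 = 67.9 on 4 df, p = 6 × 10⁻¹⁴.
- Rank-sum p = 1.00.

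**3. Power against an ordered shift, analytically.** A 1-df test with 80% power at two-sided 0.05 has non-centrality (1.960 + 0.842)² = 7.85. With the same 7.85 spread over 4 df, power is 59.5%. Reaching 80% on 4 df needs 11.94, a ratio of 11.94/7.85 = 1.52 in sample size.

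**4. Power by simulation.** 126 per arm, proportional-odds shift, 10,000 runs per row.

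| Assumed % in scores 1–5 (reference arm) | Odds ratio | Chi-square | Rank-sum | Mean-score (trend) |
|---|---|---|---|---|
| 20/20/20/20/20 | 1.8 | 53% | 74% | 74% |
| 40/30/15/10/5 | 1.8 | 50% | 73% | 71% |
| 60/25/10/3/2 | 1.8 | 45% | 69% | 64% |
| 20/20/20/20/20 | 2.0 | 68% | 86% | 86% |
| 40/30/15/10/5 | 2.0 | 67% | 86% | 84% |
| 60/25/10/3/2 | 2.0 | 62% | 83% | 78% |

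Allowing for repeat runs under similar assumptions, the ranges are about 44–54% against 67–76% (chi-square against rank-sum) at odds ratio 1.8, and 61–68% against 82–87% at 2.0. With no shift, all three tests reject in about 4.3% to 5.4% of runs.

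**5. Does a rank-sum test match the average?** Not exactly. Counts of 7/16/10/80/13 and 35/9/3/3/76 both average 454/126 = 3.60 (t-test p = 1.0), yet rank-sum gives p = 0.002. Of the ordered tests considered, the mean-score test is the one that matches a reported average.

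**The case against.** Chi-square is a valid test of whether two distributions differ at all, and it holds its type I error. It also sees what an ordered test cannot. If scores are distributed 10/20/40/20/10% in one arm and evenly in the other, chi-square has about 93% power at 126 per arm and rank-sum about 5%. For acceptability, a minority who find treatment hard to accept may be of real interest. This stands: choosing an ordered test gives something up, so the change is not free.

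The power comparison rests on assumed inputs and on the alternative that favours rank tests. The loss shrinks for larger shifts: at odds ratio 2.5, chi-square reaches about 88–92% and rank-sum 97–98%. The row speaks of acceptance of EA and names no comparison groups, whereas the blinding row above it names the EA and SA groups. This also stands. A reader might infer that a true EA–SA difference in acceptability would often be missed, but the documents support neither that comparison nor any expected effect.

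A reader might also infer that the point touches blinding. The documents do not say so. Blinding has its own row in Table 1, and the Randomization and blinding section says that assessment will be used to examine its effect on outcomes. Nothing makes acceptance a measure of blinding.

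None of this removes the mismatch between the stated average and the named test.

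**Conclusion.** The point holds as a mismatch within one table row, confirmed by the article's own rules for categorical and continuous data. The two properties of the test shown in steps 1 and 2 need no assumption about this trial: it is blind to ordering, and it is not a comparison of averages. The power loss, roughly 16 to 24 percentage points at odds ratios 1.8 to 2.0, is illustrative only. It depends on the assumed distributions, the proportional-odds shift and an assumed EA versus SA comparison.

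Severity is minor. Acceptance is a supportive secondary outcome measured once, with no bearing on the primary non-inferiority analysis or the sample size. It would go too far to call chi-square invalid here, or to say that a rank-sum test alone makes the P value belong to the average.

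**What to change.** Replace the test in the acceptance row with one that uses the ordering, and match the summary to it. There are two options:

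- Keep the average and name a mean-score (linear trend) test.
- Name a Wilcoxon rank-sum test, or a proportional-odds model, and make the score distribution and median the summary.

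In either case report counts and percentages for each of the five scores, and state which groups are compared.

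The cost is one table cell and no new data. The small statistical price is less sensitivity to differences in spread or polarisation, which the category percentages would still show.
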